### Sample size

We have not set any restrictions on participant enrollment. However, a representative sample size was calculated according to the number of newborns in the previous year in each country. Thus, we estimated a minimum sample size of 300 participants per country, based on an α-level of 0.05 and heterogeneity equal to 50%.

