#### Demographics

This questionnaire will include a subset of 14 questions about the women’s date and country of birth; state/city of residence; educational level; number of previous pregnancies; number of biological children (including stillbirths); number of people living at home (adults and children); marital status; cohabitation with partner; characteristics of the home (inside and outside spaces in square meters); and living environment changes since the beginning of the pandemic.

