##### COVID-19 coping strategies

A total of 23 items regarding potential coping strategies (problem-focused or emotion-focused) to cope with the stress related to the COVID-19 pandemic (for example, “getting a good night’s sleep”; “talking with friends”). The participants must indicate all the strategies that they are implementing [31, 32].

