### Validation of the questionnaires

We will use available validated versions of the EPDS, GAD-7 and PTSD DSM-5 checklist in the official language of all the participating countries. However, COPE-IS, COPE-IU and COPE-CF are newly developed measures, and psychometric properties are yet to be established. Scoring procedures also need to be determined. The COPE questionnaires were originally available in English and translated to Spanish and German. Thus, researchers from each country involved in the study performed the translation and cultural adaptation of the questionnaires from English into the official language of their country, following several methodological steps, defined a priori, as detailed in Table 2. No major discrepancy was identified in any of the cross-cultural adaptations.

**Table 2 Tab2:** Cross cultural adaptation of the COPE questionnaires

• Adaptation of “demographic variables”	
• Forward and backward translation from the original version	
• A pilot study with a small (*N* ≥ 4) sample of pregnant women and new mothers (to assure comprehensibility of the items as intended)	
• Revision of the instrument by an expert committee (in the perinatal field) in each country (*N* ≥ 2 persons)	

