### Data analysis

Patterns of missingness in the data will be studied and the Expectation-Maximization algorithm will be implemented to impute missing data. Attrition analyses will be carried out to examine differences between participants who completed all the assessments and those who did not. Descriptive statistics will be examined for the study variables for all the assessment times. Measurement equivalence will be studied in order to ensure we are measuring the same variables across countries.

Changes in mental health between baseline and the follow-ups will be examined by testing latent growth curve models for each outcome. Moreover, the relationships between the rates of change in predictors (i.e., risk and protective factors) and mental health results during the follow-up will be analyzed. Multilevel analyses will be performed to control the moderation of demographic variables in those interrelations. Regarding the overall fit of these models, Satorra-Bentler χ^2^, CFI, RMSEA and the confidence interval for the RMSEA statistics will be calculated. Lagrange multipliers and the Wald test will be performed sequentially to improve the fitness of the models, following the hypotheses of the study. Standardized coefficients and measurement equations with scores in R^2^ will be reported. These analyses will be undertaken using the statistical program EQS. 6.3.

To determine the risk and protective factors to predict perinatal mental health outcomes during the COVID-19 pandemic, a random sample of 70% of the data will be used to derive the machine learning algorithms including regularized logistic regression, random forest, decision tree, and gradient boosting to predict the risk of PPD, and their performance, and the remaining 30% for validation. First, in the derivation sample, all the predictors described above will be entered into the models to estimate the probability of depression or anxiety or PTSD. Beginning with a model containing all potential covariates, the variable with the least significant *P* value will be removed and tested using the likelihood-ratio test until all variables left in the model significantly (at alpha = 0.05) contribute to the model.

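### Backward elimination at 0.05 over an unreduced candidate set (102 variables at item level) would be expected to leave about five noise factors in the list that Objective 2 is meant to deliver

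*Protocol article*

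**What the plan says.** The Data analysis section sets the rule for Objective 2. "a random sample of 70% of the data will be used to derive the machine learning algorithms", with the remaining 30% for validation. In the derivation part "all the predictors described above will be entered into the models to estimate the probability of depression or anxiety or PTSD", and the least significant variable is then dropped, with a likelihood-ratio test, "until all variables left in the model significantly (at alpha = 0.05) contribute to the model". The methods named are regularized logistic regression, random forest, decision tree and gradient boosting. Optimism is to be corrected with 500 bootstrap samples.

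The predictors are described block by block. The largest COPE blocks are perinatal health care experiences (26 items) and coping ("A total of 23 items regarding potential coping strategies"). Demographics include "state/city of residence". Of the COPE questionnaires the article says "Scoring procedures also need to be determined".

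Under Sample size, "we estimated a minimum sample size of 300 participants per country", from alpha 0.05 and 50% heterogeneity, with no upper limit on enrolment. The Aim section defines the depression and anxiety outcomes for Objective 2 as new cases above the cut-off during follow-up.

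**The concern.** Objective 2 is to name risk and protective factors, and the plan goes on to scores for clinical use and nomograms. A rule that tests every described variable at 0.05 and keeps whatever is significant lets through a roughly fixed fraction of the variables that have no effect. With a long candidate list that fraction is a sizeable number of declared factors. The sample size was not set with the number of candidates or events in mind, so the unpenalised coefficients may also be unstable. A factor list that contains chance findings would feed into the tailored interventions and policy guidance that the article describes.

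**Working it through.** **The plan's own figure.** The usual formula for a proportion is n = 1.96² × 0.5 × 0.5 / e². The margin e is not stated: e = 5% gives 385, e = 6% gives 267, and 300 corresponds to e = 5.66%. So 300 cannot be reproduced without supplying e. In any case it is a precision calculation for a prevalence, not a calculation for prediction.

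**Candidates at item level.** OxCGRT 7, demographics 14, perinatal experiences 26, exposures 6, financial 2, social support 6, coping 23, emotional impact 4, health history 13, BSI-18 global index 1:

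7 + 14 + 26 + 6 + 2 + 6 + 23 + 4 + 13 + 1 = **102**.

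Items with several categories, such as place of residence, add further parameters.

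**Events.** Floor: 14 × 300 = 4200. Derivation: 0.70 × 4200 = 2940. The only rate in the article is a pre-pandemic one in five for any perinatal mental disorder. I use it, as an assumption, for baseline cases and as the upper incidence. At risk: 0.80 × 2940 = 2352.

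| Retention (assumed) | Incidence (assumed) | New cases | Per candidate |
|---|---|---|---|
| 100% | 20% | 2352 × 1.0 × 0.20 = 470 | 4.6 |
| 50% | 20% | 2352 × 0.5 × 0.20 = 235 | 2.3 |
| 50% | 10% | 2352 × 0.5 × 0.10 = 118 | 1.2 |

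**Noise factors kept.** If all 102 candidates were null, about 0.05 × 102 = 5.1 would survive. I simulated backward elimination with 102 correlated candidates (correlation 0.2, Wald test at 0.05, 60 runs per scenario). With a true odds ratio of 1.3 per SD:

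| Events per candidate | True predictors | Noise kept | True kept | Noise share |
|---|---|---|---|---|
| 4.6 | 5 | 5.7 | 5.0 | 53% |
| 4.6 | 10 | 5.4 | 9.8 | 35% |
| 4.6 | 20 | 4.6 | 18.6 | 20% |
| 2.3 | 5 | 6.1 | 4.4 | 58% |
| 2.3 | 10 | 5.6 | 8.2 | 41% |
| 2.3 | 20 | 5.5 | 14.0 | 28% |
| 1.2 | 5 | 6.3 | 3.2 | 66% |
| 1.2 | 10 | 6.1 | 6.4 | 49% |
| 1.2 | 20 | 7.0 | 11.4 | 38% |

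With an odds ratio of 1.2 and 10 or 20 true predictors, the shares ran from 22% to 60%. The noise count stays near 5 to 7 throughout. The share moves with the number of real predictors and with the power to keep them.

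**Coefficients.** In a separate simulation there were 6 true predictors (log-odds ratio 0.3 per SD), about 118 events and unpenalised backward elimination, with performance measured in new women.

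- 102 candidates: 10.8 variables kept, 5.8 of them noise; calibration slope 0.53; AUC 0.74 apparent and 0.64 in new women.
- 25 candidates: 1.1 noise variables kept; slope 0.78; AUC 0.66 in new women.

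At about 145 events the slopes were about 0.66 and 0.90. A slope below 1 means that the coefficients are too extreme.

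**The case against.** - **The count of 102 is one reading.** COPE scoring is pending, and Table 1 lists ten predictor rows. Ten domain scores would give 118/10 ≈ 12 to 470/10 = 47 events each. This stands as a qualification. But the article fixes the rule that everything described enters, and without a scoring scheme item-level entry is the natural reading.
- **The event figures are assumed and 300 is a floor.** This stands. Prevalence and incidence might both be higher: at 40% each with full retention, 2940 × 0.60 × 0.40 ≈ 706 cases, or 6.9 per candidate. The plan also imputes missing data, which may keep some records in the analysis. More events improve power and calibration, but they hardly change the number of null variables passed at 0.05. PTSD has no cut-off, so events per candidate applies to depression and anxiety only.
- **About half noise.** A reader might infer that about half of the declared factors will be noise. The documents do not support a fixed share: it depends on how many predictors are real, which is unknown, and the candidates were chosen from the literature.
- **Any selection technique.** A reader might also infer that the problem is the same whichever technique is used. It is not. Penalising all 102 candidates directly, at about 118 events, gave calibration slopes of 1.36 (ridge) and 1.24 (lasso), so coefficients were too small rather than too extreme. The noise kept also depends on tuning. Lasso at the minimum cross-validated penalty kept about 10 noise variables of 15. The one-standard-error penalty at about 450 events kept 0.1 noise and 5.6 of 6 true variables, but at about 118 events only 1.3 true ones.
- **Safeguards are planned.** Bootstrap correction, calibration checks, the 30% sample, a preference for simple models and TRIPOD reporting would expose a poorly performing score. They assess performance and do not take false factors off the list.

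**Conclusion.** The point holds in a limited form. The rule in Data analysis, applied to 102 item-level candidates, would be expected to keep about five noise factors, roughly 20–65% of those declared in scenarios with 5 to 20 true predictors. The main cause is alpha times the number of null candidates. The low event ratio, about 1 to 5 new depression or anxiety cases per candidate at the enrolment floor, is a second and separate problem: it lowers power and makes the coefficients of the unpenalised backward-eliminated model too extreme. That ratio rests on assumed baseline prevalence (20%), incidence (10–20%) and retention (50–100%), and would improve with enrolment above the floor. Neither a fixed noise share of one half nor a failure common to all the named methods can be claimed. The plan should be changed, because the rule is stated, its consequence falls on a primary objective, and the remedy is cheap.

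**What to change.** Before any outcome is examined, and without using outcome data:

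1. Replace single COPE items by pre-fixed summaries for each block, for example problem-focused and emotion-focused counts of the coping strategies, an any-exposure indicator and a mean of the distress ratings.
2. Drop state or city of residence and near-constant items from the candidates.
3. Cap the number of parameters, counting dummy variables, by the events actually available. Possible conventions, which are not in the article, are 10–15 events per parameter or an expected shrinkage of at least 0.9. At 10 events per parameter, 118 events allow about 11 parameters and 470 allow 47. Keeping all 102 would need 1020 derivation events, that is between 1020 / (0.7 × 0.8 × 1.0 × 0.20) ≈ 9,108 and 1020 / (0.7 × 0.8 × 0.5 × 0.10) ≈ 36,429 women enrolled.
4. Report item-level models as exploratory.

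The cost is revised analysis wording and a short outcome-blind data-reduction step; no new data are needed. The downside is that effects of single items within a block become exploratory.

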In regularized logistic regression models, results will be presented as odds ratio (OR) with 95% confidence intervals (CIs). The R^2^ will be used to calculate the proportion of the explained variance of clinical outcomes by the selected predictors. The different aspects of model performance will be studied, including calibration and discrimination. Calibration will be assessed using the Brier score and by plotting the non-parametric estimate of the association between the observed frequencies and the predicted probabilities. The receiver operating characteristic (ROC) curves (and the corresponding area under the ROC curve—AUC) will be calculated to test for discrimination. To correct optimism, internal validation will be performed for each model using the bootstrap procedure with 500 bootstrapped samples. The final models will be selected to derive scores for clinical use, and nomograms will be created. Criteria for this selection will include both discriminant ability (defined by the AUC) and model simplicity. Finally, the coefficients (scores) derived from the derivation cohort will also be validated in the validation cohort. These statistical analyses will be carried out in R and Python. The analyses will conform to the reporting standards of transparent reporting of a multivariable prediction model for individual prognosis or diagnosis (TRIPOD) [49].

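### Likelihood-ratio backward elimination at 0.05 is prescribed for a set of named models none of which supports it: undefined for the tree-based methods, without its nominal reference in the penalised regression

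*Protocol article*

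**What the plan says.** All of this stands in the Protocol article, Methods, Data analysis, in the part on risk and protective factors.

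- **Models.** A random 70% of the data is used to "derive the machine learning algorithms including regularized logistic regression, random forest, decision tree, and gradient boosting to predict the risk of PPD". The other 30% is kept for validation.
- **Inputs.** In the derivation sample, "all the predictors described above will be entered into the models to estimate the probability of depression or anxiety or PTSD".
- **Selection.** Elimination runs backward from the full model. At each step the weakest predictor, judged by its P value, is the one that "will be removed and tested using the likelihood-ratio test until all variables left in the model significantly (at alpha = 0.05) contribute".
- **Reporting.** "In regularized logistic regression models, results will be presented as odds ratio (OR) with 95% confidence intervals (CIs"; R² is to give the "proportion of the explained variance of clinical outcomes by the selected predictors".
- **Use.** "The final models will be selected to derive scores for clinical use, and nomograms will be created".
- **Checks.** Calibration, Brier score and AUC, 500 bootstrap samples to correct optimism, and validation of the scores in the 30% hold-out.

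**The concern.** The selection rule is fully specified: a direction, a test, an alpha and a stopping point. It is therefore not a detail left to an analysis plan. It belongs to ordinary maximum-likelihood regression, and no such model is named. The four methods that are named either have no P value to rank variables by, or have a fitted likelihood that no longer follows the reference distribution the test needs.

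The retained variables feed the reported risk and protective factors, the odds ratios, R², the clinical scores and the nomograms. An analyst would have to improvise at this step, and each way of doing so has its own fault.

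**Working it through.** The plan states no figure to reproduce here. The check sets the rule against each named model and then simulates the two readings that can be executed. Simulation inputs are assumptions unless a source is given.

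**1. Rule against model**

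- Random forest, decision tree, gradient boosting: no coefficient P values, and no nested parametric likelihood with a chi-square reference. The selection step is undefined.
- Regularized logistic regression: a likelihood exists, but estimates maximise likelihood minus penalty. Twice the log-likelihood difference is no longer chi-square with 1 df in general.
- Unpenalised logistic regression: the test is defined, but this model is not on the list.

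**2. Number of candidates**

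From the measure descriptions: OxCGRT 7, demographics 14, perinatal care 26, exposure 6, financial 2, support 6, coping 23, emotional 4, health history 13, BSI-18 index 1.

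7 + 14 + 26 + 6 + 2 + 6 + 23 + 4 + 13 + 1 = 102, if each item is entered singly.

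If all were null and independent, 0.05 per test gives 102 × 0.05 = 5.1 expected false retentions, and 1 − 0.95^102 = 99.5% chance of at least one.

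**3. Penalised reading**

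Ridge logistic regression, n = 1,000, 20 covariates with correlation 0.5, five true coefficients of 0.4, 1,500 replicates. The likelihood-ratio statistic is compared with 3.84; intervals use the inverse penalised information.

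| Ridge penalty | Null covariate rejected (nominal 5%) | 95% CI coverage of a true coefficient |
|---|---|---|
| 0 | 5.4% | 95% |
| 10 | 5.3% | 95% |
| 50 | 2.6% | 71% |
| 200 | 1.5% | 0% |

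With a light penalty little is lost. With a material one, both the 0.05 and the 95% lose their meaning. The test becomes conservative and the estimates move toward zero.

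**4. Unpenalised substitute**

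Two derivation sizes bracket the problem:

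- Full minimum sample: 14 countries × 300 × 0.70 = 2,940.
- With assumed 40% follow-up and 75% below the cut-off at baseline: 4,200 × 0.40 × 0.75 × 0.70 = 882.

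Settings: 102 candidates, 12 true with log odds ratio 0.22 per SD, correlation 0.2, Wald test standing in for the likelihood-ratio test. The 880 row shows the range over three runs (about 137 cases in one, about 154 in another).

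| Women | Noise variables kept | Inflation of retained true log-ORs | CI coverage, retained true effects | Calibration slope, new data |
|---|---|---|---|---|
| 880 | 6.0 to 6.4 | 1.47 to 1.6 | 85% to 93.5% | 0.66 to 0.70 |
| 1,500 | 5.6 | not recorded | 92% | 0.79 |
| 2,000 | 5 to 6 | 1.13 | 97.5% | 0.86 |
| 2,940 | about 5 | 1.06 to 1.07 | 96% to 97% | 0.90 |

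At 880, one run kept 12.3 variables, of which 6.0 were noise, and lost about half of the true ones. Apparent AUC was 0.84 against 0.76 in new data. Ridge on all 102 gave AUC 0.78 and slope 1.08.

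A smaller setting (60 candidates, 6 true at 0.20, 150 replicates) shows the same pattern. Noise variables kept were 3.6, 3.5 and 3.0 at n = 500, 1,000 and 2,940, with at least one in 98%, 97% and 94% of runs. The mean retained true coefficient was 0.37, 0.26 and 0.21. Intervals of retained noise variables never covered zero, which follows from selecting on significance.

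**5. Reach of the safeguards**

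The bootstrap and the hold-out estimate AUC, Brier score and calibration. Neither removes a noise variable from the list, or corrects an odds ratio or its interval.

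**The case against.** The strongest reply is that the elimination sentence speaks of one model, covariates and a likelihood-ratio test, and that the next sentence concerns logistic regression. The natural reading confines it to the regression. That is fair, and a reader who inferred that three of the four algorithms cannot be run would go too far: only the selection step is undefined for them. But the only regression named is the regularized one. The list is introduced as non-exhaustive ("machine learning algorithms including regularized logistic regression, random forest, decision tree, and gradient boosting to predict the risk of PPD"), so an ordinary logistic model is not excluded; that leads to step 4 of the working.

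Other stronger readings also fail:

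- *This is the only analysis of the second objective.* It is not. Data analysis also relates rates of change in predictors to outcomes, with multilevel analyses.
- *Elimination in the penalised model exaggerates odds ratios.* It shrinks them, and the test becomes conservative. Inflation belongs to the unpenalised substitute at small samples.
- *102 is a minimum.* The section on validation of the questionnaires leaves COPE scoring open, so items may be combined. Categorical items could raise the count.
- *The scores will perform badly.* The bootstrap, calibration checks and hold-out would largely expose that, and the AUC loss against ridge at 880 was only 0.02.
- *The plan prescribes Wald intervals, or nomograms for tree models.* It states neither. The under-coverage applies if conventional intervals are used.

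The sample-size objection also stands in part. Enrolment is uncapped, 300 per country is a minimum, and the retention and case rates behind 880 are not in the document.

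**Conclusion.** The rule as written is wrong for the models it follows, on any reading, and should be corrected before analysis. It is undefined for three methods and lacks its nominal reference in the fourth. Conventional 95% intervals in the penalised model fail by an amount that depends on a penalty the article does not state.

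If an unpenalised model is substituted, the durable harm is false retention: about 5 to 6 noise variables presented as risk or protective factors, given about 102 candidates entered singly, and fewer if COPE items are scored. Inflation of about 1.6-fold and a slope near 0.66 hold only for a derivation sample of about 880 women and 140 cases; near 2,900 women inflation is about 1.07. These sizes come from modest simulations with assumed effects and correlations. The incompatibility of rule and models does not depend on them.

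**What to change.** - Delete the backward-elimination sentence.
- Enter all candidate predictors in the penalised logistic model and tune the penalty by cross-validation inside the derivation data.
- Tune the tree-based models in the same way and report variable importance.
- Repeat all tuning, and any selection that remains, inside each of the 500 bootstrap samples.
- Show penalised coefficients without standard intervals.
- Report odds ratios with 95% intervals only from an unpenalised logistic model with a short list of predictors fixed in advance. The factors hypothesised under Aim would serve: income, social support, psychological distress, history of mental disorder, and COVID-19 exposure or diagnosis, each tied to a named item or score.

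That last model must not take all items. At about 137 cases, 137 / 102 = 1.3 cases per variable, and a run at 880 women with all 102 unpenalised gave slope 0.45 and AUC 0.735, worse than elimination in the same run (0.70 and 0.758).

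The cost is wording and analysis code, with no new data. The downside is that the prediction model holds more variables and fewer of them carry a P value.

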### Setting

This international study will be carried out in 11 European countries (Albania, Bulgaria, Cyprus, France, Greece, Israel, Malta, Portugal, Spain, Turkey and the United Kingdom), Argentina, Brazil and Chile.

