### Independent/predictor measures

#### Oxford COVID-19 government response tracker (OxCGRT)

We will collect the following macro variables related to the COVID-19 epidemiological data and public health measures publicly available for each of the participating countries from the Oxford COVID-19 Government Response Tracker (OxCGRT) [30]: (1) Population; (2) Number of confirmed deaths; (3) Number of confirmed COVID-19 cases; (4) Case fatality rate; (5) Government Stringency Index [30], a composite score from 0 to 100 that considers the strictness of containment strategies (closures, movement restrictions) and information campaigns; (6) Containment and Health Index [30], a composite measure which combines ‘lockdown’ restrictions and closures with measures such as testing policy and contact tracing, short term investment in healthcare, as well investments in vaccines; and (7) Stay-at-home requirements or household lockdowns, which include: (a) No measures; (b) Recommended not to leave the house; (c) Required to not leave the house with exceptions for daily exercise, grocery shopping, and ‘essential’ trips; (d) Required to not leave the house with minimal exceptions (e.g., allowed to leave only once every few days, or only one person can leave at a time, etc.). These data will be extracted according to the date of the baseline and subsequent follow-up analysis.

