### Significance and practical implications of the study

A previous position paper highlights that an immediate public health priority is evidence-based research on the mental health effects of the COVID-19 pandemic in vulnerable populations [22], such as women during the perinatal period [11]. Furthermore, there is an urgent need for research to address how to mitigate the mental health consequences of COVID-19 in women during the perinatal period [22].

The findings will provide critical information regarding the risk and protective factors for perinatal mental health disorders during the COVID-19 pandemic. The results of this study will offer clarification on the impact of the pandemic on women during the perinatal period, allowing the development of comprehensive models for the prediction of perinatal mental disorders, specifying the contribution of each risk and protective factor and contributing to the design of tailored interventions to support women during the COVID-19 pandemic. This will allow perinatal healthcare providers to assess women at risk of developing mental health disorders during the pandemic and provide early intervention as well as develop preventive measures. In addition, the findings of the study will assist policymakers and healthcare providers in developing guidelines and preventive interventions for perinatal mental disorders in future pandemics.

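### The AUC used to judge and select the clinical score is, on the plain reading, pooled over 14 countries with national predictors in the model, so it partly measures separation of countries rather than of women within a country

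*Protocol article*

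**What the plan says.** All references are to the protocol article.

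- **Countries.** The Setting section lists "11 European countries (Albania, Bulgaria, Cyprus, France, Greece, Israel, Malta, Portugal, Spain, Turkey and the United Kingdom), Argentina, Brazil and Chile", which makes 14.
- **National predictors.** The OxCGRT section takes "macro variables related to the COVID-19 epidemiological data and public health measures publicly available for each of the participating countries". There are seven: population, deaths, cases, case fatality rate, two policy indices and stay-at-home rules. On timing it says "These data will be extracted according to the date of the baseline and subsequent follow-up analysis". Table 1 lists them among the predictors at baseline and at all three follow-ups.
- **Model building.** Under Data analysis, the data are split 70/30 at random. All predictors enter the models in the derivation part, and non-significant ones are then removed one at a time by likelihood-ratio test.
- **Assessment and selection.** Discrimination is the ROC curve and its AUC, with 500 bootstrap samples to correct optimism. On the product: "The final models will be selected to derive scores for clinical use, and nomograms will be created". On the choice: "Criteria for this selection will include both discriminant ability (defined by the AUC) and model simplicity".
- **Use.** The section on significance and practical implications says: "This will allow perinatal healthcare providers to assess women at risk of developing mental health disorders during the pandemic".

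**The concern.** An AUC is the probability that a randomly chosen case has a higher score than a randomly chosen non-case. When data from many countries are combined, most such pairs join women from two different countries. A provider assessing women in one service never makes that comparison.

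Women assessed in the same country on the same date share every OxCGRT value, so those variables cannot order them. The variables can still raise a pooled AUC, by giving higher scores to women from countries where the outcome is more common.

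The safeguards in the plan do not address this:

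- The bootstrap corrects overfitting, and a real difference between countries is not overfitting.
- The random 30% sample is expected to contain the same countries, so it has the same excess.
- Likelihood-ratio elimination tends to keep a variable that tracks national prevalence.
- The multilevel step belongs to the growth-curve analyses, and measurement equivalence concerns the scales.

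At stake is a published discrimination figure for a clinical score that is more favourable than a user in one country would find.

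**Working it through.** **1. The plan's own figures.** The article states no AUC target and no between-country variance, so there is no AUC to reproduce. Its one computed figure is a "minimum sample size of 300 participants per country, based on an α-level of 0.05 and heterogeneity equal to 50" per cent. With n = 1.96² × 0.5 × 0.5 / e², n = 300 corresponds to a margin e of about 5.7 points. That margin is not stated. Here 300 serves only as a country size.

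**2. Share of pairs between countries.** With 14 equal countries of similar prevalence, the share of case/non-case pairs from the same country is 1/14 = 7.1%. The other 13/14 = 92.9% join different countries. Hence

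pooled AUC = (1/14) × within-country AUC + (13/14) × between-country AUC.

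**3. Simulation inputs.**

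- From the article: 14 countries, 300 women each, and a base rate of 20% (the Background's pre-pandemic figure of 1 in 5).
- Assumed: logit(risk) = logit(0.20) + country effect (SD from 0 to 1.0) + woman-level score (SD 0.5, 0.75 or 1.2).
- The true risk score is used, so overfitting plays no part. There were 100 replicates per cell.
- The within-country AUC is the mean of the country AUCs, weighted by number of pairs.

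**4. Excess of pooled over within-country AUC.**

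| Within-country AUC | SD 0 | SD 0.25 | SD 0.5 | SD 0.8 | SD 1.0 |
|---|---|---|---|---|---|
| about 0.64 | 0.000 | 0.014 | 0.049 | 0.098 | 0.131 |
| about 0.69 | 0.000 | 0.009 | 0.031 | 0.067 | 0.093 |
| about 0.78 | 0.000 | 0.004 | 0.015 | 0.034 | 0.048 |

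Base rates of 10% and 30% give nearly the same values. In the middle row at SD 0.5, country prevalences run from about 11% to 40%, and the pooled AUC is 0.724 against 0.694 within country. Step 2 then gives a between-country AUC of (0.724 − 0.694/14) / (13/14) = 0.726, and 13/14 × (0.726 − 0.694) = 0.030, which agrees with the table.

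Further runs at SD 0.5 give about 0.03 at a within-country AUC of 0.68, 0.018 at 0.74, 0.008 at 0.83 and 0.004 at 0.87.

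**5. The limiting case.** With no woman-level signal the within-country AUC is 0.500. The pooled AUC is then 0.569, 0.632, 0.698 and 0.738 at SD 0.25, 0.5, 0.8 and 1.0. This shows the mechanism and is not a forecast.

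**6. Dropping the national variables.** At SD 0.8 in the middle row, the pooled AUC falls from 0.760 to 0.677, while the within-country AUC is 0.693. Without those variables the pooled figure is slightly too low instead of too high. The mismatch lies in the measure, and removing predictors does not cure it.

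**7. Does selection go wrong?** Take logit = −1.7 + country effect (SD 0.5) + 0.6·w1 + 0.35·w2.

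- If the only candidates were w1 plus national variables and w1 plus w2, the pooled AUC would favour the first (0.698 against 0.677) in 87% of runs. Within countries it is the worse model (0.658 against 0.683).
- The stated procedure starts from all predictors. With 0.7 × 14 × 300 = 2,940 women in derivation, elimination kept w2 in 100 of 100 runs. With 882 women it kept w2 in 97 of 100.
- The full model had the highest pooled AUC in 60 of 60 runs (mean 0.715, against 0.696 and 0.677). A separate rerun put it first in 90–100% of runs, with no loss within countries.

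**The case against.** **Pooling is not stated in words.** This is true, and a within-country AUC would also fit the article's wording. But a random split of the whole data set, an AUC for each model and no mention of country in this step lead a reader to the pooled figure. The predictor set, the selection criterion and the clinical use are all fixed in the text, and the mismatch arises from their combination. It is not just a detail left to an analysis plan.

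**The effect may be small.** This stands. The models include BSI-18 distress, which is close in content to the depression and anxiety outcomes, as well as mental health history and social support. A within-country AUC above 0.8 is plausible, and the excess at SD 0.5 is then below 0.01. The simulation also lets the model know each country's effect fully, which is an upper bound on what seven national variables can carry.

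**OxCGRT values change with date.** This also stands. They can order women in one country who were assessed at different times, but not women assessed on the same date.

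**National context is legitimate in a risk score.** This stands as well. The article names these variables as study factors, and they can inform absolute risk. A reader might infer that they should be left out of the nomogram, but the documents do not support that as a correction. It is a trade-off.

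**A reader might infer that the plan will choose a model with poorer woman-level predictors.** The two-model comparison in step 7 suggests it, but the stated elimination procedure would not normally produce that pair. The article also selects on simplicity.

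**Conclusion.** The concern holds as a mismatch between the measure and the use. A pooled AUC with national predictors in the model overstates separation of women within a country whenever countries differ in prevalence and those predictors carry the difference. The planned internal validation cannot reveal it.

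In the cells with woman-level signal the excess ranges from 0 to about 0.13. It is about 0.03 or less at SD 0.5 once the within-country AUC reaches 0.68. These sizes rest on an assumed between-country SD and an assumed woman-level signal, neither of which the article gives. Comparing countries is a secondary objective, so differences are at least contemplated.

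Selection of a worse model within countries is a possibility, not a demonstrated result. The point is a cheap improvement to how the score is judged and does not invalidate the prediction analysis.

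**What to change.** Define the AUC used to judge and select the clinical score as within-country concordance: count only case/non-case pairs from the same country and combine them over countries with stated weights, for example the number of pairs. Apply this in both the derivation sample (with the bootstrap correction) and the validation sample. Report the pooled AUC as secondary. The OxCGRT variables may stay in the models.

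The cost is one sentence of text and a few lines of code. The headline AUC will be slightly lower if countries differ. Single-country estimates will be imprecise in small countries: at the minimum of 300 women, the validation part holds about 0.3 × 300 = 90, with about 0.2 × 90 = 18 cases at a 20% rate and fewer after attrition. The combined figure should therefore drive selection, with the country values shown for information.
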